### Sample size

The sample size for this study was determined using the Superpower [46] package in R 4.5.3 software. The primary outcome measure for this study is the total score on the Star Cancellation conventional subtest of the BIT, and the primary analysis strategy will be analysis of covariance (ANCOVA). We used the threshold for a clinically significant effect size measure proposed by Székely et al. (d = 0.61) [47]. A test-retest correlation during treatment of *r* = 0.63 (R^2^ = 0.40), was estimated using raw data from the supplementary materials of Vilimovsky et al. [48], using their results from the Bells cancellation test as a reasonably close proxy. Thus, assuming an alpha of 0.05, 80% power, d = 0.63, and a R^2^ for covariates of.40 requires a sample size of 27 per group. Because of local feasibility concerns when studying this population, we believe it is unlikely it would be possible to collect more than 25 participants per group. Thus, we lowered our threshold for statistical power to 70%, which requires a minimum sample size of 21 per group as our target. Although 80% power is commonly treated as a benchmark, power between 70% and 90% remains within accepted norms [49]. Consistent with recommendations that sample size in constrained clinical populations should reflect the maximum feasible recruitment under real-world conditions [50], our target sample also takes into consideration practical feasibility. The R script with our power analysis is included in the supporting information materials S3 File.

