### Randomization

Covariate-adaptive randomization, as described by Sella et al. [51], will be used to assign participants to treatment conditions. Randomization is stratified based on neglect severity, assessed using the BIT [42]. Specifically, participants will be considered as having “mild” neglect if they fail fewer than 3 subtests on the BIT, or when only functional symptoms are reported. Participants will be considered as having “moderate to severe” neglect when they fail 3 or more subtests on the BIT. Severity classification will be completed by a blinded assessor. Participants will be assigned to one of two groups in a manner that balances neglect severity between groups, to control for potential baseline differences in symptom severity. Randomization will be conducted by a member of the research team who is not involved in data collection or analysis and provided to the assigned Trainers immediately before the “training” visit (i.e., home or inpatient visit #2).

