### Statistical analyses

Given the heterogenous nature of neglect, deficits may not be captured by a single task; therefore, a battery of subtests was selected to assess functioning across multiple areas (e.g., functional and paper-pencil tasks). Subtest-level analyses will capture deficits and improvements across different areas of functioning. Note that the study has a single primary outcome (Star Cancellation subtest of the BIT); thus, the strongest evidence of the trial’s efficacy will be determined from this a-priori outcome. Secondary outcomes will have weaker evidential value but may remain useful for future meta-analyses and to inform future research.

To assess the effectiveness of the PTM intervention on neglect severity over time, data will be analyzed using analysis of covariance (ANCOVA) using generalized linear modelling with the glm() function in R software. We are interested primarily in two mean differences: (a) changes from pre-PTM (T0) to immediate post-PTM (T1) and (b) changes from pre-PTM (T0) to 1-month post-PTM (T2). Because mean differences from T1 to T2 are assuredly smaller than comparisons to baseline, our study would be underpowered to detect them, so we have elected to calculate only the primary comparisons of interest. In the first ANCOVA analysis, the outcome will be at T1, and predictors will include T0 scores and time post-stroke as covariates, and Condition (5-degree vs. 15-degree goggles) as a between-subjects factor. In the second ANCOVA analysis, the outcome will be at T2, T0 scores, time post-stroke, and follow-up assessment timing will be used as covariates, and Condition will again be a between-subjects predictor. In the second analysis, follow-up assessment timing will be included to assess whether differences in timing for post-treatment assessments impacts treatment outcomes.

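### Allocation is balanced on a BIT severity class that neither ANCOVA includes; adding it costs almost nothing and may recover a few points of power

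*Protocol article*

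**What the plan says.** Under Randomization, the protocol article uses covariate-adaptive allocation and states that "Randomization is stratified based on neglect severity, assessed using the BIT". A participant counts as mild "if they fail fewer than 3 subtests on the BIT, or when only functional symptoms are reported", and as moderate to severe with three or more failed subtests. The stated aim is to keep severity balanced between the groups.

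Under Statistical analyses, the terms of both models are listed. For T1, "predictors will include T0 scores and time post-stroke as covariates, and Condition (5-degree vs. 15-degree goggles) as a between-subjects factor". For T2, the covariates are the T0 score, time post-stroke and one more: "follow-up assessment timing will be used as covariates, and Condition will again be a between-subjects predictor". The reason given is that "follow-up assessment timing will be included to assess whether differences in timing for post-treatment assessments impacts treatment outcomes". The severity class is in neither list.

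Under Sample size, the target rests on reduced power: "we lowered our threshold for statistical power to 70%, which requires a minimum sample size of 21 per group as our target".

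**The concern.** A factor used to force balance between arms is normally carried into the analysis. Balancing removes that factor's contribution to the real sampling variation of the treatment difference. If the model omits the factor, its variance stays in the residual and the reported standard error is larger than it should be. Confidence intervals are then too wide and the test rejects slightly too seldom. This trial has already accepted 70% power, so even a small avoidable loss is worth a look.

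The baseline outcome score is only a partial stand-in. The class counts failures over the BIT subtests, and Star Cancellation is one of them. Inclusion criteria admits people with two failed BIT subtests of any kind, or on caregiver ratings alone. Statistical analyses expects many perfect Star Cancellation scores and notes that one task may miss deficits. Two participants with near-ceiling Star scores can therefore fall in different classes.

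A second, lesser matter is that follow-up timing in the T2 model becomes known only after randomisation. Conditioning on such a variable can, in some circumstances, distort a randomised comparison.

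**Working it through.** **Inputs from the Sample size section.** Alpha 0.05 (two-sided assumed; not stated), covariate R² = 0.40, 21 per group for 70% power and 27 for 80%. The effect size is given first as d = 0.61 and then as d = 0.63 in "assuming an alpha of 0.05, 80% power, d = 0.63, and a R^2^ for covariates of.40 requires a sample size of 27 per group".

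**Input not in the document.** How much the class predicts beyond T0 score and time post-stroke. I assume a partial R² of 0 to 0.10 in the formula and a residual class effect of 0 to 0.6 SD in the simulation.

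**Formula.** Power from the noncentral t with df = 2n − 2 − k, where k is the number of covariates, and noncentrality = d / √(1 − R²) × √(n/2).

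**Step 1: reproduce the plan's figures.** With d = 0.61, R² = 0.40 and k = 2:
- n = 21: 0.61/√0.60 × √10.5 = 2.552, df = 38, power 70.1%.
- n = 27: 0.61/√0.60 × √13.5 = 2.894, df = 50, power 81.0%.

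These are the smallest n that reach 70% and 80%, so 21 and 27 are reproduced. With d = 0.63 the same formula gives 20 and 25. I therefore use 0.61; the two printed values should be reconciled, but that is a separate matter.

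**Step 2: add the class (k = 3, df = 37, n = 21).** Total R² = 0.40 + 0.60 × partial R².

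| Partial R² of class | Total R² | Noncentrality | Power without class | Power with class |
|---|---|---|---|---|
| 0 | 0.400 | 2.552 | 70.1% | 70.0% |
| 0.02 | 0.412 | 2.578 | 70.1% | 70.9% |
| 0.05 | 0.430 | 2.618 | 70.1% | 72.2% |
| 0.10 | 0.460 | 2.690 | 70.1% | 74.5% |

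At partial R² = 0.10 the standard error shrinks by a factor √0.90 = 0.949, about 5%. With a class that adds nothing, 70% power still needs 21 per group.

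**Step 3: simulation of the Gaussian model** (n = 42, 10,000 runs per case, two equal strata, balanced allocation within strata standing in for the covariate-adaptive scheme, d = 0.61).

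| Residual class effect | Power without class | Power with class |
|---|---|---|
| 0 | 67.4–67.6% | 66.9–67.0% |
| 0.3 SD | 66.2–67.4% | 66.8–67.5% |
| 0.6 SD | 63.8–65.4% | 67.7–68.2% |

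The mean estimate is 0.60 to 0.61 in every case, so omission causes no bias. At 0.6 SD the type I error without the class is 4.0–4.6%, which is conservative. The powers are lower than in Step 2; the comparison within each row is what matters.

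**Step 4: timing in the T2 model** (second simulation, true effect 0.61).

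| Timing differs by arm | Shared cause with outcome (coefficient) | Without timing | With timing |
|---|---|---|---|
| No | None | SE 0.247, power 67.7% | SE 0.250, power 66.2% |
| No | 0.5 | power 67.8% | power 69.6% |
| 0.3 SD | None | estimate 0.61, power 68.0% | estimate 0.61, power 65.7% |
| 0.3 SD | 0.5 | estimate 0.61 | estimate 0.55 |
| 0.6 SD | 0.5 | estimate 0.61, power 67.5% | estimate 0.49, power 48.0%, type I error 7.5% |

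Bias appears only when timing both differs by arm and shares a cause with outcome.

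**The case against.** The strongest reply is that the models already adjust for the baseline value of the outcome, itself a BIT subtest, and for time post-stroke, so little of the class's information may be left. This stands in part. With no residual class effect omission costs nothing, and at 0.3 SD the difference is negligible. The article also refers readers to an R script that is not shown, but the printed term lists are explicit and should be right in themselves.

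Four stronger readings are tempting and not supported:
- A reader might infer that omitting the class biases the treatment effect or inflates false positives. In the Gaussian model it does neither.
- A reader might infer a larger gain. Raising total R² to 0.45 or 0.50 would give 73.7% or 77.7% power, but the class would have to explain 0.05/0.60 = 8% or 0.10/0.60 = 17% of the remaining variance. Nothing in the article supports such values, and the second lies outside the range used here.
- A reader might infer that adjusting for timing biases the T2 result. Nothing in the article says timing differs by arm, and the 4 to 6 week window limits how far it could. The unblinded Trainer handles scheduling, but the text does not say whether that covers assessment visits, which are assigned to the blinded Assessor. If timing is related to outcome but not to arm, adjustment gains precision.
- A reader might infer that the stated purpose of the timing term requires a Condition-by-timing interaction. The text speaks of an impact on treatment outcomes, which a main effect can address. An interaction would also be very imprecise with 42 participants.

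**Conclusion.** The point holds as a minor one. The class that drives allocation is missing from both ANCOVAs. The consequence is a possible loss of precision, not bias: about 0 to 4.5 points of power over an assumed partial R² of 0 to 0.10 (70.1% to 74.5% at the upper end). Including a class that adds nothing costs about 0.1 point by formula and about 0.5 point in the simulation. The facts are certain. The size is not, because the article gives no figure for the prognostic value of the class beyond the T0 score. All calculations are for the Gaussian model; the negative binomial alternative was not examined. The timing matter is secondary and conditional. It calls for a sensitivity analysis and does not show the planned T2 model to be wrong.

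**What to change.** Add the severity class, coded as used for allocation (mild versus moderate to severe), to the T1 and T2 ANCOVAs, keeping T0 score and time post-stroke. Secondary outcomes generally follow the same procedures, so the term can carry over to them. In addition, report the T2 effect once without follow-up timing, as a sensitivity analysis beside the planned model. The cost is one line of model specification and one extra fit. The class is already determined for every randomised participant, no sample size changes, and the change can be fixed in advance because data collection is still under way.

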#### Secondary outcomes.

Secondary outcomes will include the remaining conventional subtests of the BIT [42], three behavioural BIT subtests (menu reading, article reading and picture scanning) [42], one subtest of the Eschenbeck Standardized Activity of Daily Living Test (SADL; *filling out a form*) [63], the Halifax Neglect Impact Scale (self- and caregiver-reported measures assessing the frequency and impact of neglect symptoms on ADLs), the Hospital Anxiety and Depression Scale [64] and the Fatigue Severity Scale [65]. Each of these secondary outcomes will be administered at all three assessment time points.

Feasibility and acceptability data will also be collected at T1 (i.e., within one week of training) via a Patient Exit Interview, using a modified version of the Intrinsic Motivation Inventory [66] which includes 38 Likert scale questions and 8 open-ended questions about usability and enjoyment of the PTM software.

To measure PA after-effects, a modified Proprioceptive-and-Visual Straight-Ahead (mPVSA) task (described below) will be administered immediately after each training session.

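### The Star Cancellation ANCOVAs are valid, but they use only the T0 Star score as baseline severity and leave a nearly free gain in precision from the rest of the T0 BIT unused

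*Protocol article*

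**What the plan says.** Under Statistical analyses, the T1 model is fixed in the text: "predictors will include T0 scores and time post-stroke as covariates, and Condition (5-degree vs. 15-degree goggles) as a between-subjects factor". The T2 model has the same terms plus the timing of the follow-up assessment. Primary and secondary outcomes generally follow the same procedure, so the natural reading is that each outcome is adjusted for its own T0 value.

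Under Secondary outcomes: "Secondary outcomes will include the remaining conventional subtests of the BIT", and "Each of these secondary outcomes will be administered at all three assessment time points". The other conventional subtests are therefore measured at T0. Under Inclusion criteria, impairment on two BIT subtests and/or caregiver ratings confirms neglect. Under Randomization, the number of failed BIT subtests (fewer than 3, or 3 or more) sets the severity class.

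Under Sample size, the covariate R² rests on one correlation: "A test-retest correlation during treatment of *r* = 0.63 (R^2^ = 0.40), was estimated using raw data". The 80% target is given as "assuming an alpha of 0.05, 80% power, d = 0.63, and a R^2^ for covariates of.40 requires a sample size of 27 per group". The article then says "we believe it is unlikely it would be possible to collect more than 25 participants per group", and so "we lowered our threshold for statistical power to 70%, which requires a minimum sample size of 21 per group as our target".

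**The concern.** The article's own statements suggest that one T0 Star score may be a thin measure of baseline severity.

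- Statistical analyses expects many perfect Star scores and says that a single task may not capture a participant's deficits.
- The inclusion rule admits people on any two impaired BIT subtests and/or caregiver ratings, so a participant can enter with an unimpaired Star score. Among such people, T0 Star says little about who is worse.
- With R² = 0.40, 60% of the outcome variance is left unexplained.

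Power was lowered to 70% because more participants are not expected. When sample size is the constraint, baseline data already in hand are the obvious remaining source of precision. What is at stake is a few points of power on the primary comparison, and somewhat narrower intervals.

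**Working it through.** **Inputs from the article (Sample size; Statistical analyses).** Alpha 0.05, taken as two-sided because that reproduces the stated sizes; d = 0.61 as justified and d = 0.63 as printed in the calculation; covariate R² = 0.40; 21 per group; k = 2 covariates at T1.

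**Formula.** Noncentral t with ncp = d/√(1 − R²) × √(n/2) and df = 2n − 2 − k.

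**Step 1: reproduce the plan (k = 2, R² = 0.40).**

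| d | n per group for 80% | n per group for 70% | Power at 21 per group | Power at 25 per group |
|---|---|---|---|---|
| 0.61 | 27 | 21 | 70.1% | 77.8% |
| 0.63 | 25 | 20 | 72.9% | 80.4% |

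For d = 0.61 at 21 per group: ncp = 0.61/√0.60 × √10.5 = 2.552, df = 38. The stated 27 and 21 match d = 0.61 exactly and do not match d = 0.63, so 0.61 is used below.

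**Step 2: add one continuous T0 BIT covariate.** Let ρ be its partial correlation with the outcome, given the covariates already in the model. Then R²_new = 0.40 + 0.60ρ², k = 3 and df = 37. The article gives no value for ρ, so the range is an assumption.

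| Assumed ρ | R²_new | ncp | Power at 21 per group | Gain over 70.1% (points) |
|---|---|---|---|---|
| 0 | 0.400 | 2.552 | 70.0% | about −0.1 |
| 0.1 | 0.406 | 2.565 | 70.5% | 0.4 |
| 0.2 | 0.424 | 2.604 | 71.8% | 1.7 |
| 0.3 | 0.454 | 2.675 | 74.1% | 4.0 |
| 0.4 | 0.496 | 2.784 | 77.4% | 7.3 |

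Under the present model, 22, 23 and 25 per group give 72.2%, 74.2% and 77.8%. Values of ρ of 0.2, 0.3 and 0.4 are therefore worth roughly one, two and four participants per group. The standard error shrinks by the factor √(1 − ρ²): 0.980, 0.954 and 0.917.

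**Step 3: cost if the covariate is useless.** Power falls from 70.09% to 70.03%, under 0.1 point. A rise in R² of about 0.001 offsets this.

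**Step 4: which ρ is conceivable?** With a T0–T1 Star correlation of 0.63, suppose the composite correlates a with T0 Star and b with T1 Star. Leaving time post-stroke aside, ρ = (b − 0.63a)/√((1 − 0.63²)(1 − a²)). For a = b = 0.4, 0.5 or 0.6, ρ = 0.21, 0.28 or 0.36. For a = 0.6 and b = 0.5, ρ = 0.20. These are illustrations; the article reports neither a nor b.

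**The case against.** The strongest reply is that nothing here is wrong. Adjusting for the baseline value of the outcome and time post-stroke is standard and unbiased, it matches the basis of the sample size, and it delivers the stated power. That stands.

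Three further objections also stand in part:

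- **Unknown gain.** At ρ = 0 or 0.1 the gain is nil or 0.4 points.
- **Ceiling argument.** Primary outcome says that Star Cancellation was chosen for being more sensitive than other paper-and-pencil tasks. Less sensitive subtests may be at ceiling in the same people, which weakens the case for ρ in the upper part of the range.
- **Missing components.** A composite is missing when any component is, and the article uses listwise deletion below 5% missing. Losing one participant takes the planned 70.1% to 69.0%, which would consume much of the 1.7 points gained at ρ = 0.2. A baseline-imputation rule removes this cost.

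The analysis script in S3 File is not at hand and may hold further detail. It does not undo a covariate list stated in the text.

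A reader might infer that the trial is unable to reach 80% power and that the present model is to blame. The article does not support this. It calls more than 25 per group unlikely, not impossible, and with the printed d = 0.63, 25 per group would give 80.4%.

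**Conclusion.** The point holds as a missed efficiency option: the T0 Star score is the only severity covariate in the stated models, and other severity data from the same battery are collected at T0. It is neither an error nor a bias, and a reader should not take it to mean that the primary analysis is invalid or falls short of its stated power.

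For ρ from 0 to 0.4, the change in power at 21 per group runs from a loss of under 0.1 point to a gain of 7.3 points. This rests on d = 0.61, R² = 0.40 for the existing covariates together, two-sided 0.05, the gaussian model and complete data. Nothing in the article fixes ρ within that range. No gain has been shown for the negative binomial model, which the BIC rule may select. The recommendation rests on the imbalance between a negligible cost and a plausible gain, not on a demonstrated loss.

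**What to change.** Before any unblinded analysis, prespecify one additional continuous covariate in both Star Cancellation models (T1 and T2): the T0 total of the remaining conventional BIT subtests. Keep the T0 Star score and time post-stroke, and follow-up timing at T2. Use one composite; entering each subtest separately is not sensible with 42 participants. Put it in both the gaussian and the negative binomial candidate, so that the BIC comparison is between models with the same covariates.

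State how the total is formed, and give a simple imputation rule for a missing T0 component that uses baseline data only, so that nobody is dropped for it. State as well which of d = 0.61 and d = 0.63 was used in the sample size.

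Cost: one residual degree of freedom (38 to 37 at T1, under 0.1 power point), one more term in the analysis code, and a protocol modification to be reported with the results, since data collection is under way. No new data, visits or participant burden.

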To address these barriers to the clinical application of PA procedures, a home-friendly, game-like PA software called Peg-the-Mole (PTM) was developed. In this protocol, participants wear prism goggles and are prompted to touch as quickly as possible a target bull’s eye held by a cartoon mole presented on an iPad. In comparison to typical PA procedures, PTM requires minimal supervision because the software provides automated instructions, feedback, and data recording, allowing participants to complete sessions independently once trained. The program’s game-like interface enhances engagement and motivation. Importantly, PTM incorporates an adaptive algorithm that adjusts target presentation time based on individual performance, encouraging rapid, ballistic movements and minimizing conscious self-correction during pointing. This algorithm promotes the spatial realignment processes underlying PA while reducing the need for specialized equipment (e.g., occlusion boards). Taken together, these features increase accessibility by enabling standardized, engaging delivery of PA in various settings [36].

Initial testing of PTM was conducted in a sample of healthy young adults comparing it to a typical PA procedure using 15-degree rightward-deviating goggles [36]. Results indicated that prism exposure during PTM yielded adaptation and significant after-effects of equivalent magnitude to those observed with a typical PA procedure. Importantly, participants found PTM to be more enjoyable and engaging than the typical PA procedure. Further PTM studies with both healthy young and older adult samples demonstrated that 15-degree prism goggles induced significantly larger after-effects than 5-degree goggles [39]. Additionally, after-effects induced by PTM have generalized to aspects of wheelchair maneuvering (e.g., a significant reduction in the number of right-sided hits), providing evidence that PTM has the potential to generalize to more functional tasks [40]. More recently, a pilot study examined the feasibility of implementing a desktop version of PTM with stroke patients in an inpatient rehabilitation unit. PTM was administered daily for 10 sessions over two weeks by occupational therapists and the protocol was generally found to be feasible and engaging [41]. In the present study, we adapted PTM for iPad administration to enhance flexibility and accessibility for at-home use.

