To support the future clinical implementation of PTM, the primary objective of the present study is to examine PTM’s effectiveness in reducing neglect symptoms as measured by the Star Cancellation task of the Behavioural Inattention Test (BIT) [42]. Short-and longer-term effectiveness will be examined in terms of symptom reduction (i.e., does the PTM PA protocol improve neglect symptoms over time?). We hypothesize that participants who complete 10 sessions of PTM PA treatment using 15-degree rightward-deviating goggles will show a greater reduction in the severity of neglect symptoms immediately after training and at one-month follow up, compared to participants using the PTM protocol with 5-degree deviating goggles.

Secondary objectives include (1) examining treatment effects across additional neglect measures, as well as measures of ADLs, (2) evaluating feasibility and acceptability, (3) examining the magnitude of PA after-effects and the relationship between these effects and neglect severity, and (4) exploring changes in psychological outcomes. First, we will examine whether the 15-degree PTM condition leads to broader improvements in neglect symptom severity across additional neglect assessments, as well as improvements in ADL functioning over time. Second, we will evaluate the feasibility and acceptability of using the iPad-based PA treatment in both inpatient and community settings. Feasibility will be assessed based on compliance with the treatment protocol and schedule, while acceptability will be evaluated through patient feedback. PA after-effects (mean difference in degrees of visual angle from pre- to post-PTM) will be measured after each treatment session. We will examine whether the 15-degree condition produces larger after-effects compared to the 5-degree condition. Additionally, we will investigate whether the magnitude of PA after-effects predicts neglect severity. The relationships between neglect severity and psychological variables, including anxiety, depression, and fatigue, as well as changes in these psychological outcomes following participation in the PTM protocol will also be explored. Although fatigue, anxiety, and depression are prevalent post-stroke [43,44], their association with spatial neglect remains underexplored, and these secondary analyses will provide insight into the broader impact of PTM and whether improvements in neglect symptoms may be associated with changes in psychological outcomes and fatigue severity.

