To examine the impact of after-effects, a single average score over the two weeks of prism adaptation will be calculated. Then, we will examine the relationship between these mean after-effects scores and condition using an unequal-variances t-test. We will also explore the Pearson correlation between mean after-effects scores and the primary outcome.

An intention to treat analysis will be completed. We will also examine outcomes of participants who complete at least 80% of training and assessment components. Given the nature of our follow-up procedures, we expect low dropout. If missing data < 5%, listwise deletion will be used (complete cases) as when there is minimal missing data, more advanced strategies generally perform equivalently to listwise deletion [68]. If there is substantial missing data, it will be handled using multiple imputation using the Jomo [69] and mitml [70] packages in R software. In such a case, we will evaluate whether missing data is associated with any measured variables to incorporate into the missing data model.

All protocol deviations will be documented and reported to the principal investigator. Deviations that could affect participant safety will be promptly communicated to the ethics board. All deviations will be reviewed to assess impact, and corrective and preventative actions will be implemented as necessary to minimize recurrence.

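### The planned after-effect/outcome correlation cannot separate an individual-level relation from two arm differences; a within-condition estimate should stand beside it

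*Protocol article*

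**What the plan says.** The Introduction lists, under the third secondary objective, two separate questions: whether 15-degree goggles give larger after-effects, and a second one, "we will investigate whether the magnitude of PA after-effects predicts neglect severity".

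The Statistical analyses section reduces the after-effects to one value per participant ("a single average score over the two weeks of prism adaptation will be calculated"), compares that value between conditions with an unequal-variances t-test, and then states: "We will also explore the Pearson correlation between mean after-effects scores and the primary outcome". Nothing more is said about this correlation. The adjustment for T0 score, time post-stroke and Condition is described in the same section, but only for the two ANCOVAs.

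The protocol expects Condition to act on both variables. For after-effects, the Introduction reports that in earlier studies of healthy adults "15-degree prism goggles induced significantly larger after-effects than 5-degree goggles". For the outcome, the hypothesis is that the 15-degree group "will show a greater reduction in the severity of neglect symptoms immediately after training and at one-month follow up".

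**The concern.** A Pearson correlation takes two variables and no covariates. Computed over all 42 participants, it mixes two things: the relation between a participant's after-effect and outcome within an arm, and the displacement of one arm from the other on both axes. If the arms differ on both variables, the second component alone gives a non-zero correlation.

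The question about prediction could then be answered yes when the result only restates the t-test on after-effects and the ANCOVA on outcome. A reader would probably take a positive correlation as evidence of mechanism, or as a sign that after-effects identify responders. The pooled figure cannot support that by itself.

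Baseline severity is a second, separate problem. The sample-size section assumes "A test-retest correlation during treatment of *r* = 0.63 (R^2^ = 0.40", so about 40% of the variance of a follow-up score is baseline. Any link between after-effects and T0 would pass into an unadjusted correlation with T1.

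**Working it through.** **Inputs.** From the Sample size section: 21 per group, alpha 0.05 (taken as two-sided), d = 0.61 on the outcome, baseline to follow-up correlation 0.63. Not in the document: the after-effect gap between arms, written *a*, in within-arm SDs. It is an assumption, shown over a range. The simulations use normal data. Signs are set so that larger after-effects and better scores are both positive; scoring misses instead of hits flips the sign and not the size.

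**Step 1: the plan's own figure.** ANCOVA F test with noncentrality λ = N(d/2)²/(1 − R²), d = 0.61, R² = 0.40:
- 27 per group: λ = 54 × 0.0930/0.60 = 8.37, power 0.81.
- 21 per group: λ = 42 × 0.0930/0.60 = 6.51, power 0.701.

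Both stated sizes reproduce as the smallest that reach 80% and 70%. The section also prints a different d: "assuming an alpha of 0.05, 80% power, d = 0.63, and a R^2^ for covariates of.40 requires a sample size of 27 per group". With d = 0.63 the sizes would be 25 and 20, so 0.61 is used below. The choice matters little here.

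**Step 2: correlation produced by the arms alone.** With equal arms and zero within-arm correlation, in within-arm SD units, the covariance is (a/2)(d/2) and the variances are 1 + a²/4 and 1 + d²/4. Hence

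r = [a/√(a² + 4)] × [d/√(d² + 4)].

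For d = 0.61 the second factor is 0.61/√4.3721 = 0.292, which is also the upper limit of r. Then:
- a = 1: 0.447 × 0.292 = 0.13
- a = 2: 0.707 × 0.292 = 0.21
- a = 3: 0.832 × 0.292 = 0.24

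The critical |r| at N = 42 is 0.304, so the induced r is on average below the threshold. What changes is how often chance carries it over.

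**Step 3: how often it is significant.** 20,000 simulated trials, 21 per arm, no within-arm relation, d = 0.61:

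| Analysis | a = 1 | a = 2 | a = 3 |
|---|---|---|---|
| Pooled Pearson with T1 | 12.9% | 26.9% | 35.5% |
| Pooled Pearson with T1 − T0 change | 16.3% | 34.1% | 45.6% |
| Partial, T0 only | 17.9% | 39.2% | 52.0% |
| Partial, T0 and Condition | 5.0% | 5.0% | 4.9% |

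Reading the outcome as a change score, or adjusting for T0 alone, does not help. Both remove outcome noise and make the arm difference show more clearly. Adjustment for Condition is what restores 5%.

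**Step 4: dependence on a real arm effect.** With d = 0.3 the pooled rates fall to 7.3%, 10.0% and 12.3% for a = 1, 2, 3. With d = 0 they are 4.8 to 5.1%.

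**Step 5: the baseline route.** With no treatment effect, an assumed within-arm correlation *q* between after-effect and T0 appears at T1 as 0.63 × q: q = 0.2, 0.3, 0.5 gives 0.13, 0.19, 0.32.

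**The case against.** **The sentence does not say pooled, raw or T1.** This is correct. The article refers to an R script in its supporting information (S3 File), which is not shown and might stratify or adjust. A reader might infer that the plan definitely pools the arms and uses the raw score; the text does not state either. One unqualified correlation does most naturally read as pooled, and Step 3 shows that the change-score reading has the same problem.

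**It is exploratory and decides nothing.** This stands. The section says the strongest evidence comes from the single primary outcome, and no threshold or conclusion is tied to the correlation. The separate t-test will also show readers how far the arms lie apart on after-effects.

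**The inflation needs a special scenario.** The treatment must work, and must work without any individual-level link to after-effects, although the Introduction presents after-effects as the therapeutic route. This stands as a limit on the size. It does not remove the ambiguity, because the pooled figure cannot show which scenario holds.

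**Conditioning on Condition changes the question and costs power.** This is the strongest point. The objective does not say within condition. Prism strength is what manipulates after-effects, so if they mediate the effect, adjustment discards real signal. Simulating full mediation with a total effect of d = 0.61, power at a = 3 is about 63 to 65% for the pooled correlation and about 36 to 38% adjusted for T0 and Condition; at a = 2 it is 80% and 73%. A reader might infer that the pooled correlation should be dropped. The documents do not support that, and both estimates have a use.

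**Conclusion.** The point holds, as a moderate one about an exploratory analysis. As worded, the correlation cannot distinguish an individual-level relation from two arm differences. On the protocol's own hypotheses and design effect, with no within-arm relation and an assumed after-effect gap of 1 to 3 SD, the induced correlation is about 0.13 to 0.24, and the false-association rate about 13 to 36% against a nominal 5%.

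This rests on three things: the natural reading of the sentence as pooled and unadjusted, an after-effect gap that the document does not give, and a true outcome difference between arms. Without the last, the inflation is absent. A reader might infer that the test is invalid in all circumstances, or that the efficacy result is compromised. Neither follows: the size is nominal when the outcome does not differ by arm, and the primary ANCOVA already includes T0 and Condition.

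**What to change.** Keep the pooled Pearson correlation, labelled descriptive, and state its time point and whether it uses the score or the change. Beside it, report a linear regression of the T1 Star Cancellation score on mean after-effect, T0 score and Condition, and the same for T2. Give the within-condition association with its confidence interval, and make it the basis for any statement that after-effects predict neglect severity. Add a rank-based version (partial Spearman) as a sensitivity check, since the section itself expects skew and many perfect scores. If the S3 script already does this, the text should say so.

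The cost is about one line of R per time point and no new data. Data collection is still ongoing, so the change can be fixed before results are known. The downside is a less precise estimate, which under mediation leaves out the between-arm part; this is why both figures should be shown.
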